### Development of the intervention package

The findings of the baseline survey was disseminated in 2011 to all the stakeholders at the central level (focal person from Ministry of Health, Director General from Department of Health Services, Director of Family and Child Health Division) and district level (District Public Health Officer, Public Health Nurse, Focal Persons, Local Leaders, Media) by organizing a dissemination meeting at central and district level. Feedback was collected about the possible interventions to address the different barriers identified. The implementation package was also discussed with teams from the World Health Organization. The findings of the baseline study can be found in Nepal Public Health Foundation website (http://www.nphfoundation.org).

In dialogue with the representatives of Government of Nepal, Family Health Division, a model of community mobilization was developed that could be scaled up within the existing health system, which focused on enabling SBA attendance at birth, and strengthening links to be developed between communities and health facilities. An intervention package was developed that fits the national policy of engaging female community health volunteers (FCHVs), Health Facility Management Committee (HFMC), and Youth Groups to increase utilization of SBA services.

### Interventions

The intervention package has five components and a diverse set of activities which aims to overcome the barriers in scaling up SBA services in Nepal.

1. Lack of Family Support for the Pregnant Women to Reach a Facility for Childbirth.

2. Lack of Funds to for a Women and Families to Seek Childbirth Care with a SBA.

3. Unavailability of Transportation to a Facility for Childbirth.

4. Lack of Women-friendly Environment in Health Facilities.

5. Issues of Security of SBA.

A team from the Nepal Public Health foundation coordinates the activities. There are team leaders for each of the three districts. Each VDC has a research assistant responsible for proper implementation of the intervention package and on-site monitoring of all activities during the intervention period. An extensive training had been given to the district level team (includes district coordinator in district and research assistant at VDC level) to implement the intervention package.

### Component 1: Increased family support for pregnant women to reach a facility for childbirth

FCHVs were oriented by project staff to discuss with pregnant women and members of their families the importance of birth with a skilled attendant, and review with the family the birth and emergency preparedness card which the pregnant woman completes in her antenatal care visits.

There are mothers group under each FCHV in each ward. Mothers groups were given an orientation by FCHVs with the support of project staff to invite the families of identified pregnant women (identified in each ward through FCHVs and mothers group members) to regular meetings to discuss the importance of birth with a skilled attendant and family member’s support to the pregnant women to reach the health facility and to access childbirth care with a SBA. The mothers groups provide information to the family members about the emergency fund and transportation arrangement mechanisms discussed below.

### Component 2: Availability of funds to support pregnant women and families to seek childbirth care with an SBA

Currently in Nepal, mothers groups have funds which can be utilized for any health related purposes and regarded as an emergency fund. The research team organized discussions with the HFMCs of each Health Post, Sub Health Post regarding the operation of an emergency fund by the mothers groups. The discussion included the roles and scope of the HFMC to support mothers groups in operating the fund and possible modalities for its operation, particularly how to protect against losses and replenishment of the fund. The project staff supported the HFMC in their discussions with mothers groups for the expansion of the current fund, to agree upon a modality of operation and to establish regular coordination and feedback between the HFMC and mothers group. All mothers group agreed to use the existing fund as an emergency fund to support women to reach health facility which is supposed to be reimbursed by the women after getting the incentives from health institution as a part of the Safe Delivery Incentive Program in Nepal.

### Component 3: Availability of transportation to a facility for childbirth

The project staff interacted with the HFMC of all intervention VDCs to discuss the development of a system to organize transportation of mothers for reaching facilities for childbirth and in case of complications. The possibility to mobilize local actors, particularly local youth groups and mothers groups, was discussed. There was also a discussion on the modality and functioning of the system.

Project staff supported the HFMC to organize a meeting with youth groups to discuss the transport needs of pregnant women to reach health facilities for childbirth and in case of complications. The Youth groups agreed to support. Members of the HFMC periodically organize meetings with the youth groups to review the activities, discuss any problems faced and possible solutions.

### Component 4: Development of a Women-friendly environment in health facilities

The HFMC oriented the SBAs and staff on improving the friendliness of the facility for pregnant women and their families. Furthermore, training on communication skills was also given to the SBAs and staff of each facility. Meetings were organized with the health facility management committee and with providers to discuss the policy to allow a companion of the women’s choice during childbirth. SBAs were oriented on how to work with the companion during labour and birth.

### Component 5: Establishment of mechanisms to improve security of SBAs

As the security of female SBAs was identified as one of the barriers to ensuring service availability, meetings were organized with the HFMCs, mothers groups, youth groups and other relevant actors in the community to discuss the situation and agree upon the mechanisms to improve the security situation of SBAs. For arriving to the facility at night, SBAs will be accompanied by a member of the youth groups or a FCHV of the particular area of a village during childbirth.

### Measuring the impact of the intervention package

Data on the primary outcomes of the project will be collected through periodic surveillance and an end line survey (evaluation phase) in all VDCs of project. For the evaluation to begin in May 2014, Surveyors will administer questionnaires to the women in intervention and non-intervention VDCs. Qualitative research will be conducted to evaluate the process indicators. The questionnaires will be the same used during the baseline phase of project with the primary and secondary outputs indicated below. The surveyors and data analyst will be blinded for the evaluation phase.

### Primary output

Utilization of SBA services by the women for childbirth.

### Secondary output

Ante-natal care visits for 4 times by pregnant women

Post natal care visits of mothers and babies

Availability of transport to the women to visit health institutions for childbirth

Functional operation of emergency fund

Security of SBA

Family support to the women for childbirth at health institution

Women friendly health facility environment

### Project time line

Intervention preparation: October, 2012

Formation of steering committee, preparation for trainings: November to January, 2013

Meeting and training: February, 2013

System of transportation and Emergency fund establishment:February to April, 2013

Intervention:May, 2013 to April, 2014

Evaluation of project: May to October, 2014

The evaluation of the impact of intervention will be done using multiple methods. Both the qualitative and quantitative methods will be used in evaluation. End line survey to determine the effects of the interventions will be done with key process indicators. This will include questionnaire surveys with 5000 women in 36 VDCs in three districts.Health workers, female community health volunteers, youth group members, health facility management committee members will be interviewed.

The instruments used for the base line survey will be used for the evaluation of outcome. Necessary modifications will be made to the instruments.Data will be entered in Epi data and imported to SPSS for analysis. Results from the bivariate and multivariate analysis will be compared with the baseline results. Intervention and control VDCs will be compared to identify any difference in the outcome variables to find out the association of the intervention components for possible change. Test of significance will be done at 5% significance level using appropriate statistical test.

### Interim analysis

A mid-term data monitoring will be conducted during the mid-intervention phase in 2013. For this a data management committee will be formed. The data management committee will report how well the project has been implementing. They will check the key methodological component of project; whether enrolment has been adequate, whether randomization has been done. End line survey will serve as evaluation of project. The evaluation phase will have preparation of evaluation tools, recruitment of enumerators and supervisors which will help in interim data analysis. This team will also check the completeness in the implementation of intervention data, adherence to the ethical principles and will advise for the improvement in intervention phase in case of detected opportunities for improvement.

### Analysis strategies

Data will be double entered into EpiData 3.1, validated using Epi Info data compare, and will be transferred to SPSS 16 for analysis. The findings from quantitative tool will be presented in tabular and graphical forms. To control for more than one confounding variable multivariate logistic regression model will be applied. For statistical inference of the result, a confidence level of 95% is set. For the analysis process of qualitative data collected form FGD, the transcription of taped FGD session will be typed and reviewed thoroughly then translated in English language by field coordinators. The content of transcription will then be labeled as per the domain of analysis.

Missing data will be characterized in terms of the degree and patterns of missing data. For imputation of missing value of categorical variables, the frequency distribution will be used as the basis for randomly generating a value for each observation lacking a response. For example, if education was measured in three categories -- “less than high school” (25% of complete data cases), “completed high school” (40%), or “more than high school” (35%) -- then for each observation with education missing, a random number between 0 and 1 will be drawn from a uniform distribution and the missing value replaced with “less than high school” if the random number is less than or equal to 0.25, “completed high school” if the number is greater than 0.25 but less than or equal to 0.65, or “more than high school” if greater than 0.65. For imputation of numerical variable regression method is used.

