**Method/Design:**

This study involves a cluster randomized controlled trial involving approximately 5000 pregnant women in 36 clusters. The 18 intervention clusters will receive the following interventions: i) mobilization of family support for pregnant women to reach the health facility, ii) availability of emergency funds for institutional childbirth, iii) availability of transport options to reach a health facility for childbirth, iv) training to health workers on communication skills, v) security provisions for SBAs to reach services 24/24 through community mobilization; 18 control clusters will not receive the intervention package. The final evaluation of the intervention is planned to be completed by October 2014. Primary study output of this study is utilization of SBA services. Secondary study outputs measure the uptake of antenatal care, post natal checkup for mother and baby, availability of transportation for childbirth, operation of emergency fund, improved reception of women at health services, and improved physical security of SBAs.

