### Study design

The implementation research underway is to test the impact of interventions designed to address the main barriers to utilization of SBA services at birth identified in the baseline study. The study design is a cluster randomized controlled trial. The three districts (Bajhang, Dailekh and Kanchanpur) were the three strata and the VDCs from each stratum serve as clusters which were allocated for intervention and control by *randomization*. A baseline survey was conducted in 2011 in all 50 VDCs of the three districts. All women with under-5 children from each VDCs were included.

The three districts of Far and Mid-west Nepal represent three ecological zones –- Kanchanpur is Terai or a lowland belt stretching east to west in the south; Dailekh is Hills; and Bhajang is a mountainous areas. Selection of three districts was based on ecology with low human development index. The population inhabiting these districts is varied, representing different ethnic groups [31]. Terai district is mainly inhabited by aboriginal population of Nepal the Tharus; the mid hills by Kshetri and Bahun (Aryan upper cast but lower economic status). The mountain district has predominantly Mongoloid populations. These districts have lower indicators with respect to education, health and economic development.

The implementation of intervention covers 36 of the 50 VDCs of the three districts (22 VDCs of Bajhang, 10 VDCs of Dailekh and 4 VDCs of Kanchanpur (see table in Figure 1). VDCs having a rate of utilization of SBA at birth higher than the national target of 60% were excluded from the intervention. In order to have an even number of clusters, one more VDC with coverage of 57% was excluded.

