### Sample size estimate

The study includes all pregnant women in the 36 VDCs. It is estimated that at least 110 births per year will occur in each VDC and that the proportion of births assisted by a SBA is 36% [7]. The sample size was estimated assuming that the intervention and control groups and the unmatched clusters were of approximately equal size. A value of k -the between-cluster coefficient of variation – to be equal was estimated in the intervention and control groups. All estimates are based on a two-tailed 5% significance level. The value of k is likely to be 0.25 on the basis of estimates of the SBA utilization rate according to the baseline survey [24]. Hence, It was estimated that on at least 110 pregnant women in each cluster with 36 clusters would be required for the period of one year to detect a 10% difference in SBA utilization rate with 80% power and 95% confidence level.

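### The only inferential model the protocol names takes no account of randomisation by VDC or of the district strata, although the sample size allows for between-VDC variation

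*Protocol article*

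**What the plan says.** **Design.** Under Study design, the three districts are the strata, and "the VDCs from each stratum serve as clusters which were allocated for intervention and control by" randomisation. The clusters are "22 VDCs of Bajhang, 10 VDCs of Dailekh and 4 VDCs of Kanchanpur", 36 in all. The abstract gives 18 intervention clusters and adds that "18 control clusters will not receive the intervention package".

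**Sample size.** The Sample size estimate section allows for clustering: "The value of k is likely to be 0.25 on the basis of estimates of the SBA utilization rate according to the baseline survey". It takes 36% SBA use and at least 110 births per VDC per year, and sets the trial "to detect a 10% difference in SBA utilization rate with 80% power and 95% confidence level". On the test it states: "All estimates are based on a two-tailed 5% significance level".

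**Analysis.** Analysis strategies names one model: "To control for more than one confounding variable multivariate logistic regression model will be applied". It is to be run in SPSS 16 with 95% confidence. Project time line plans bivariate and multivariate analyses of a survey of 5000 women, and adds: "Test of significance will be done at 5% significance level using appropriate statistical test". The same paragraph says that the VDCs of the two arms will be set against each other on the outcome variables, but gives no method for doing so. Neither section mentions a random effect, generalised estimating equations (GEE), robust variance, a design effect, a VDC-level summary or district as a stratum.

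**The concern.** The sample size treats women in the same VDC as correlated. The model named for the analysis, taken as written, treats them as independent. The protocol therefore pays for clustering in recruitment and then does not carry it into inference. A logistic model without a cluster term counts about 5000 women as independent pieces of evidence when only 36 units were randomised.

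At stake are the p-value and confidence interval for the primary output, use of SBA services at birth. The Discussion says that the Ministry of Health has committed to national scale-up if the package is proven effective, and Benefits to control areas says this would start with the control VDCs. A test that rejects far more often than 5% when the package does nothing is a poor basis for that decision.

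**Working it through.** **Inputs from the protocol.** p = 0.36, k = 0.25, at least 110 women per VDC, 18 VDCs per arm, a 10% difference (read as 36% against 46%), two-sided 5% and 80% power (Sample size estimate, abstract). Study design gives about 110 women per VDC in Bajhang and Dailekh and about 310 in Kanchanpur. Reading 310 as per VDC gives 32 × 110 + 4 × 310 = 4,760, in line with the stated figure of around 4800.

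**Step 1: reproduce the 36 clusters.** The unmatched cluster formula is

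c = 1 + (1.96 + 0.84)² × [p0(1−p0)/m + p1(1−p1)/m + between-cluster variance] / (p0−p1)².

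Hold the between-cluster SD at k × p0 = 0.25 × 0.36 = 0.09 in both arms:

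- within-VDC part: (0.2304 + 0.2484)/110 = 0.00435
- between-VDC part: 2 × 0.09² = 0.0162
- c = 1 + 7.85 × 0.02055/0.01 = 17.1, so 18 per arm and 36 in all.

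This matches the plan. With independent women the same target needs only 379 per arm, or 379/110 = about 3.4 VDCs. The stated 36 therefore appear only if clustering is counted. (Applying k = 0.25 proportionally in both arms at 36% and 46% gives c = 21.15, or 22 per arm. That is a separate matter and does not affect this point.)

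**Step 2: intracluster correlation and design effect.**

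- ICC = k² × p/(1−p) = 0.0625 × 0.36/0.64 = 0.0352.
- Equal clusters of 110: DE = 1 + 109 × 0.0352 = 4.83; √4.83 = 2.2.
- Planned mix: size-weighted mean m = (32 × 110² + 4 × 310²)/4,760 = 162.1; DE = 1 + 161.1 × 0.0352 = 6.66; √6.66 = 2.6.

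**Step 3: true error of a nominal 5% test that ignores VDC.** Error = 2 × [1 − Φ(1.96/√DE)].

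- 110 per VDC: 37.3%.
- 4800 women in equal VDCs (133 each): DE 5.65, 41.0%.
- 5000 women in equal VDCs (139 each): DE 5.85, 41.8%.
- Planned 110/310 mix: 44.8%.

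**Step 4: simulation check.** There were 3,000 null trials with beta-binomial outcomes, randomised 11/11, 5/5 and 2/2 within districts. Logistic regression without a cluster term rejected in 38.0% (equal sizes) and 45.5% (planned sizes). A plain two-sample t-test on the 36 VDC proportions rejected in 4.8% to 5.5%. Adding district terms to the logistic model gave 38.2% and 44.6%. The simulation contained no true district differences, so those last figures show only that district terms do not replace a VDC term.

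**Step 5: sensitivity to k.** The residual k after district adjustment is not given in the protocol, so the values below 0.25 are assumptions. All use p = 0.36, and ranges run from 110 per VDC to the planned mix.

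| k | ICC | Design effect | SE too small by | True error |
|---|---|---|---|---|
| 0.25 | 0.0352 | 4.83–6.66 | 2.2–2.6 | 37–45% |
| 0.20 | 0.0225 | 3.45–4.62 | 1.9–2.1 | 29–36% |
| 0.15 | 0.0127 | 2.38–3.04 | 1.5–1.7 | 20–26% |
| 0.10 | 0.0056 | 1.61–1.91 | 1.3–1.4 | 12–16% |

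**The case against.** A reader might infer that the protocol prescribes ordinary, unclustered logistic regression on individual women as its primary between-arm test. It does not say so. Neither the absence of a cluster term nor the unit of analysis is stated, the sentence gives confounder control as its purpose, and nothing calls it the primary analysis. Individual-level fitting is the natural reading, because the survey covers 5000 women and the imputation example concerns a respondent's education. It remains an inference. An unseen analysis plan could supply the cluster adjustment, and a condensed article may leave such detail out.

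Project time line also leaves the test open and does speak of comparing VDCs between arms. That has to be acknowledged, but it identifies the groups being compared and names no cluster-level method.

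A reader might also take 37% to 45%, or standard errors more than twice too small, as unconditional. Both depend on k. The protocol calls 0.25 only likely and does not say whether it is a within-district figure. Baseline use ran from 33% in Bajhang to 64% in Kanchanpur, and VDCs above 60% were excluded. If k was taken across districts or before that exclusion, the variation left within districts could be smaller.

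What does not stand is the view that this is mere silence. The article goes as far as software version, a named model and imputation cut-points. Having chosen to name a model, it names one that, as written, does not match its own design and sample size.

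**Conclusion.** The point holds in conditional form. As written, the named model and the unspecified test do not account for randomisation by VDC or for the district strata, while the sample size does allow for between-VDC variation. If the model is fitted to the women's records without a cluster term, the true error of the nominal 5% test is about 37% to 45% at the plan's own p and k. It is about 12% to 36% if residual k lies between 0.10 and 0.20. These figures rest on p = 0.36, on 310 being a per-VDC count in Kanchanpur, and on k describing the variation left after any covariates. The documents do not show that the investigators intend to ignore clustering. They show that following the stated model literally would do so, which warrants correction before the endline data are analysed.

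**What to change.** Name one primary analysis that respects the design. For example: compare VDC-level proportions of births with an SBA between arms, stratified by district, using a t-distribution with about 36 − 3 − 1 = 32 degrees of freedom, and report the risk difference with its 95% confidence interval.

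Keep the confounder-adjusted logistic model as a secondary analysis, fitted with VDC as the cluster (GEE or a mixed model, with a small-sample correction) and district as a covariate. Before naming the procedure, confirm that the chosen software provides the correction.

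Treat secondary outputs measured on individual women, such as antenatal and postnatal visits, in the same way. Outputs that turn out to be measured per facility or per VDC, possibly the emergency fund, SBA security or the facility environment, should be analysed at that level.

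The cost is revised analysis wording, slightly more analysis work and wider, valid confidence intervals. Recruitment, intervention and survey are unchanged, provided each record identifies its VDC. The article does not state this, but a survey organised by VDC makes it a reasonable assumption.

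### The rule for missing categorical values (one random draw from the marginal distribution) does not exempt the yes/no primary outcome and ignores arm; applied to that outcome as written, it shrinks the treatment difference by the missing fraction

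*Protocol article*

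**What the plan says.** The rule is in the protocol article under Analysis strategies. Its scope is general: "For imputation of missing value of categorical variables", with no variable named as excluded, "the frequency distribution will be used as the basis for randomly generating a value for each observation lacking a response". The example that follows is a covariate, education in three categories. Its shares are taken from the complete records (the first category is "25% of complete data cases"), then "a random number between 0 and 1 will be drawn from a uniform distribution" and compared with cut-offs at 0.25 and 0.65. That is one draw per missing value from one distribution. Arm, district, VDC and other variables play no part.

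Numerical variables are treated differently: "For imputation of numerical variable regression method is used". Use of other variables to predict a missing value is therefore named only for them.

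The primary output is "Utilization of SBA services by the women for childbirth", which Sample size estimate handles as a proportion of births, so it is a yes/no variable. Under Project time line, "Intervention and control VDCs will be compared to identify any difference in the outcome variables".

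**The concern.** This is a stated method, not a detail left to another document. A value drawn without regard to arm carries no information about the intervention. When it stands in for a missing primary outcome, it adds the same expected rate to both arms and moves them closer together. This happens even when values are missing for reasons unrelated to the outcome, a case in which leaving those births out does no harm to the estimate.

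There are two further consequences. The filled values enter the analysis as if they had been reported, so the uncertainty about them is ignored and the result depends on one set of random numbers. And a single marginal distribution disregards differences that the article itself reports: baseline attendance ran from 33% in Bajhang to 64% in Kanchanpur (Background).

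The estimate matters because the article says that national scale-up depends on the package being found effective.

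**Working it through.** The plan gives no missing fraction and no figure for the effect of imputation, so there is nothing of its own to reproduce. The check takes its design figures and shows a range for the missing fraction.

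**Inputs**
- Control proportion p0 = 0.36 (Sample size estimate).
- Difference to detect: 10%, read as 10 percentage points, so p1 = 0.46 (same section).
- 18 clusters per arm (Abstract), 110 births per cluster, and between-cluster coefficient of variation k = 0.25, equal in the two arms (Sample size estimate).
- f, the fraction of primary outcomes missing: not given. Assumed 5%, 10% and 20%, equal in both arms, with missingness unrelated to the outcome within arm.

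**Expected difference**

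With equal arms the pooled observed rate is (0.36 + 0.46)/2 = 0.41, and every filled value has this expectation in either arm. So

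E[p_arm] = (1 − f)·p_arm + f·0.41

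and the f·0.41 term cancels in the difference:

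E[difference] = (1 − f)·(p1 − p0).

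| f | Control | Intervention | Difference | Odds ratio |
|---|---|---|---|---|
| 0 | 0.3600 | 0.4600 | 0.100 | 1.51 |
| 5% | 0.95×0.36 + 0.05×0.41 = 0.3625 | 0.95×0.46 + 0.05×0.41 = 0.4575 | 0.095 | 1.48 |
| 10% | 0.90×0.36 + 0.10×0.41 = 0.3650 | 0.90×0.46 + 0.10×0.41 = 0.4550 | 0.090 | 1.45 |
| 20% | 0.80×0.36 + 0.20×0.41 = 0.3700 | 0.80×0.46 + 0.20×0.41 = 0.4500 | 0.080 | 1.39 |

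At 2% missing the difference is 0.98 × 10 = 9.8 points. With unequal missingness, 5% in control and 15% in intervention, the pooled rate is (0.95×0.36 + 0.85×0.46)/1.80 = 0.4072. The difference is (0.85×0.46 + 0.15×0.4072) − (0.95×0.36 + 0.05×0.4072) = 0.090.

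Using observed births only, each arm's expectation stays at 0.36 and 0.46, so the difference stays at 10 points for every f.

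**Simulation** (18 against 18 clusters of 110, beta-binomial with k = 0.25, 4,000 runs, cluster-level t-test)
- Pooled draws: mean difference 0.099, 0.090 and 0.080 at f = 0, 10% and 20%, in line with the formula.
- Draws made within arm: 0.101 and 0.099 at 10% and 20%, so no shrinkage. But the rejection rate rose from 72% with nothing missing to 79% and 81%, while the standard deviation of the estimate did not fall (0.0374, then 0.0377 and 0.0397). Information was lost, yet the test rejected more often: this is the cost of counting filled values as observed.

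**Power under pooled draws**

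Power = Φ(d·√(17/V) − 1.96), with 17 = 18 − 1. For filled data, d = 0.10(1 − f) and V = [p0*(1 − p0*) + p1*(1 − p1*)]/110 + (1 − f)²·k²·(0.36² + 0.46²), where p* are the table's rates. For observed births, d = 0.10, the first term of V uses 0.36 and 0.46 with 110(1 − f) births, and the second term is not shrunk.
- f = 10%: 71.3% filled, 72.2% observed births only.
- f = 20%: 69.1% filled, 71.2% observed births only.

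With nothing missing the same formula gives 73.0%. How that compares with the planned 80% is a separate matter. The loss of power is modest because the estimate and its spread shrink together; the harm is mainly to the estimate.

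**The case against.** The imputation text never mentions the primary outcome. Its only example is a covariate, in a section whose only named model is a logistic regression for confounders. Nor does it say that the complete cases are pooled across arms. If draws were made within arm, or only covariates were filled, the shrinkage would not occur. A reader might infer that the plan commits outright to imputing SBA use from a pooled distribution. The text does not say so. It sets a rule for categorical variables without exception and illustrates it with one distribution that ignores arm. The inclusion of the outcome and the pooling are the plain reading of that rule, not explicit statements.

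The size is also uncertain. Outcomes come from home interviews with consenting women, and nothing says that records will be created for women who were not interviewed. The relevant f may therefore be non-response to one question, which could be a few percent. This stands: nothing in the article supports 20%, and at 2% to 5% the difference falls only to 9.8 to 9.5 points.

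Two other inferences go too far. One is that the total error always points to no effect; if missingness depends on the outcome differently in the two arms, its direction is not fixed. The other is that the numerical rule understates spread; the article names regression without saying whether a random residual is added.

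What remains is that the rule as written allows a harmful use on the primary outcome, and that one marginal draw treated as data is a poor method for any variable.

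**Conclusion.** The point holds as a conditional one. Followed as written, the rule reaches the binary primary outcome and ignores arm, and the expected difference is then (1 − f) times the truth. This rests on draws pooled across arms, missingness at random within arm and, for the exact factor, equal f in both arms. Under those conditions observed births alone give an unbiased estimate, so the rule makes matters worse than not imputing. The bias is small at a few percent missing and grows in proportion to f, which the article does not give.

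If only covariates are filled, the randomised comparison is not attenuated. The cost is then weaker covariate adjustment, because drawn values are unrelated to everything else about the woman. In either use, filled values are analysed as though observed.

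**What to change.** In Analysis strategies:

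1. State that the random-draw rule is not applied to outcomes. If it was meant for covariates only, say so.
2. Analyse the primary outcome on births with observed attendance, and add a sensitivity analysis for missing outcomes. Its form is the sponsor's choice.
3. Where imputation is used, replace the single marginal draw with multiple imputation whose model includes arm, district, VDC and the outcome. Arm and district are constant within a VDC, so VDC would enter as a random effect beside them.

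The cost is a change of wording and slightly more analysis work. No further data are needed.
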